### 2.9. Standard care

Standard care is based on the national guidelines includes regular outpatient visit at a minimum of once a year, treatment with an antipsychotic agent (>80% of those with standard care on one or the other antipsychotic agent), a once-a-year general check-up with blood samples including metabolic markers, among other things. This varies, however, according to individual patient need.

### 2.10. Instructors

The instructors are healthcare professionals such as counselors, physiotherapists or nurses with experience in physical interventions, and/or dance teachers (bachelor’s in dance pedagogy) with experience of meeting patients with mental health issues. Before starting the intervention in the main study, the instructors will attend a 1-day course regarding the target-group as well as the intervention administered by the research team. During this course, the instructors will receive practical instructions about the movement sessions according to the standardized program design and how to work with the target-group safely, supportively and ethically. The course will also cover shortly the theoretical background of schizophrenia and the mechanisms through which the intervention aims to improve the clinical, physiological and emotional condition of the target group. Written and digital informational material will be distributed by the research team. The material will be distributed not only with documents but also with informational videos made by the research team. The intervention coordinators will provide information regarding the practical components, choreography, and modifications as well as recorded movement exercises.

### 2.11. Procedures

When a patient at the psychiatry clinic is interested in participating in the main study, contact information will be transferred from responsible clinician to doctoral student, who will call the participant, give further information, answer questions if needed, and check inclusion/exclusion criteria. A meeting at the movement laboratory at the hospital will be set up with participant and psychiatrist who will do the PANSS, CGI-S, CDSS, and PSP as well as the doctoral student who will conduct physical tests and measures and test cognitive function combined with functional brain imaging and eye tracking. The baseline measures will take about 2.5 h with a break in between. Data on gender, age, years of education, way of living, years with schizophrenia diagnosis, medication, and smoking will be collected but no other sociodemographic information. The baseline measurements will be conducted 4 to 2 weeks prior to the beginning of the intervention. It may take a few weeks to form a group, and therefore, a 2-week window for the baseline data collection is needed. The participant will be instructed about the accelerometer, which is to be worn for 7 days to evaluate everyday activity. After baseline measures are finished, sealed envelopes will be given to the participants to randomize whether they will be part of the control or intervention group. The participants in the intervention group will be shown videos of the instructors and the training studio, to enable recognition and feeling of safety.

At session 2, 12, and 23 motion capture will be recorded. Those sessions will take place at the movement laboratory. Participants and one instructor will wear small reflex balls on six points: hands, elbows and knees, while doing the training session. Setting up will be done by an engineer at the movement laboratory or the doctoral student. On week 6 of the intervention the same procedure of tests, apart from the accelerometer, cognitive tests and functional brain imaging, will be repeated. After the last session, about two participants and their family members or other next of kin from each group will be purposefully selected for interview. The get a heterogenic group, we will strive for a variation regarding age, gender, participation rate and severity of disease. The participants and their family member or other next of kin will receive written and oral information about the qualitative study (including assurance of voluntariness and confidentiality), before signing a written consent. After finishing the intervention at week 12 all tests from baseline will be repeated in 1–2 weeks. This will also be done after 6 and 12 months, excluding the accelerometer.

The pilot study was conducted in the same way, except there was no control group or randomization procedure nor cognitive or brain imaging measures, nor will there be any follow-up tests in 6 or 12 months.

### 2.12. Locations

The intervention will most often take place in a training studio at the psychiatric clinic, an environment well known and safe to the participants. In detail, this applies to session 1, 3–11, 13–22, and 24. Sessions 2, 12, and 23 are conducted in the Laboratory of Motion Analysis at the Örebro University Hospital which is equipped with the EEG-fNIRS and Motion Capture devices. The same locations were used for the pilot study.

### 2.13. Frequency and duration

The duration of the biweekly movement intervention will be 60 min, the order and content of which is described in detail in Table 1. Throughout the intervention period, the participants will be encouraged to practice their favorite movement or relaxation techniques at home between the sessions if they want to. Each of the three parts of the intervention will be recorded, and the research team will distribute video-links upon request to the participants if they want to have support in practicing on their own at home. Moreover, when a participant fails to attend a session, an email with the video-link will be sent out, with encouragement to practice at home and keep up the frequency of two sessions a week.

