**Methods:**

The study is a mixed-method randomized controlled trial to evaluate the effects of a 12-week intervention for adults with schizophrenia. The treatment group (30 participants) will receive the intervention in addition to standard care and the control group (30 participants) only standard care. The intervention consists of 24 biweekly sessions with a duration of 60 min. The pre-test (weeks from 4 to 2 prior to the intervention) and post-test (week 12) include clinical measure (PANSS), quality of life, social performance, movement quantity, brain function and eye tracking measures. In addition, a treatment subgroup of 12–15 participants and their family member or other next of kin will complete a qualitative interview as a part of their post-test. Two follow-up tests, including clinical, quality of life, brain function and eye tracking will be made at 6 and 12 months from the completion of the intervention to both study groups. The primary outcome is change in negative symptoms. Secondary outcome measures include general and positive symptoms, quality of life, social performance, movement quantity, brain function and eye tracking. Explorative outcome includes patient and family member or other next of kin interview.

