### 2.7. Sample size

The sample size is calculated according to the primary outcome PANSS. For the primary outcome (improved negative symptoms according to PANSS after 12 weeks), the total number of required study participants was calculated (Curcic et al., 2017). Calculation was based on a minimum improvement of 15% on total PANSS score between the intervention and control group. With a power of 80% and a significance level of 0.05, we calculated the sample size to be *N* = 60 (30 intervention + 30 control participants), including a 25% dropout rate.

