### 2.15. Adherence

Intervention adherence will be noted by the instructors during both pilot study and main study. To stimulate high adherence to the intervention throughout all the intervention time period, we will work in close collaboration with the clinic, both for reminding about the importance of intervention participation during the 12 weeks and in practical issues regarding getting to the studio in time. To keep the creative physical exercise sessions motivating and interesting, the focus will be on enjoyment, social inclusion and increasing body movement in harmony with music. In addition, the fact that the intervention consists of three different parts with separate themes will hopefully stimulate adherence motivation. To retain as many participants as possible, reminder text-messages and emails will be sent to participants. Notes about participants who discontinue or deviate from the study will be made.

Randomization will minimize bias, but we will assess any change in the treatment plan of the participants including medication, if they stop taking their medication and become ill, or if they change to a better medication and improve because of the intervention.

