## 4. Ethics and dissemination

The study is conducted in accordance with the standards of Good Clinical Practice and in agreement with the Declaration of Helsinki. Written informed consent will be provided by the research team. The information letter includes written information about the study, the purpose and procedures, the voluntary nature of participation, and the option to withdraw at any time. If needed, clinicians will help to clarify the written information. The participants are guaranteed confidentiality and that their data are stored on a secured server except the brain imaging data, which will be made anonymously public. It is impossible to identify the participants from the brain imaging data, and at the same time, open science is supported by publishing the data. The participants will be informed about the public data sharing on a group level without any personal information in their information letter and asked for their consent for it. In addition, the participants in the study were invited to an information meeting before the start of the study, where verbal explanations of all the procedures were given. Any adverse events or harm arising from study participation will be reported and managed by the instructors and the research team in accordance with ordinary healthcare routines.

Data are collected in both pen-and-paper and digital formats and securely stored at the University Health Care Research Center. The questionnaires and tests will be pretested on a conditions-appropriate group during the pilot study to determine whether the wording and length of the questionnaire and tests were appropriate for the study’s target group. The pilot study investigated different aspects of intervention fidelity. No unauthorized persons have access to the collected data, during the study, apart from the brain imaging data as mentioned above. All the data collected are coded to protect the study participants’ identification. All data and the code list are stored securely and separately to prevent unauthorized persons from having access to them.

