## 5. Adverse event and safety monitoring

Instructors in the study will regularly ask participants in the intervention how they felt after the previous session. Any adverse events related to the participation in intervention will be recorded and assessed in terms of severity which will be reported to the principal investigator, serious adverse events will be recorded in the patient’s medical chart.

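### The one active harm question stated is tied to the previous session, so it does not reach session 24, a leaver's last attended session, or home practice

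*Protocol article*

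**What the plan says.** Section 5 (adverse events and safety monitoring) describes how harms are sought: "Instructors in the study will regularly ask participants in the intervention how they felt after the previous session". It then says what is kept: "Any adverse events related to the participation in intervention will be recorded and assessed in terms of severity". Section 4 adds a general undertaking: "Any adverse events or harm arising from study participation will be reported and managed by the instructors and the research team". It gives no schedule for asking.

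Section 2.13 gives the response to a missed session: "when a participant fails to attend a session, an email with the video-link will be sent out, with encouragement to practice at home", so that the twice-weekly pace is maintained. The same section encourages home practice throughout the 12 weeks and offers video links to participants "if they want to have support in practicing on their own at home". On those who leave, section 2.15 says: "Notes about participants who discontinue or deviate from the study will be made".

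Table 2 has no adverse-event item at baseline, week 5–7, week 12, month 6 or month 12.

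**The concern.** Instructors see participants at sessions. A question about the preceding session, put by an instructor, can be answered only by someone who has come to a later one. Harm can itself keep a participant away, so the chance of being asked depends on something that harm affects. Home practice is not a session in this sense, and the final session has no successor.

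Two things are at stake. The first is the harm count in the intervention arm, which would tend to be too low because physical harms in these situations would surface only if volunteered. The second is the reading of absence and dropout. Feasibility is among the trial's objectives, and the Discussion wants to learn whether the format influences motivation and retention. Without a recorded reason, intolerance of the programme cannot be told from low motivation.

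**Working it through.** This is mainly a comparison of passages, with a little arithmetic.

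**Inputs**
- Sessions: "The intervention consists of 24 biweekly sessions with a duration of 60 min" (Abstract, Methods), held twice a week for 12 weeks (section 2.2).
- Intervention arm: 30 participants (sections 2.2 and 2.7).
- Dropout: the sample size is given as "including a 25% dropout rate" (section 2.7).
- Attendance rate: none is given.

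**Reproducing the plan's figure.** 12 weeks × 2 = 24 sessions, as stated.

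**Reach of the question at full attendance.** A session can be asked about only if another follows: 24 − 1 = 23 of 24 sessions at most. Session 24 has no later session.

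**Reach for a leaver.** Someone whose last attended session is the k-th they attended can be asked about at most k − 1 of those k sessions. The one left out is the session after which they stopped coming.

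**Number of leavers.** 0.25 × 30 = 7.5, so 7 or 8 people. This assumes that the 25% applies to this arm and that all of it falls within the 12 weeks; section 2.7 says neither.

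**Overall proportion.** Everyone has exactly one last attended session, either session 24 or an earlier one. At full attendance that is 30 of 30 × 24 = 720 participant-sessions, or 4.2%. The proportion is small. The concern is which sessions are missed, not how many.

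**Missed sessions and home practice.** With no attendance rate and no count of home sessions, neither number can be computed.

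**Other routes by which harm could surface**

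| Situation | Stated harm question | Other stated route |
|---|---|---|
| Any session followed by another attended one | Yes (section 5) | Recording under sections 4 and 5 |
| Session 24 | None | Week 12 clinician ratings; interview for a subset |
| Last attended session of a leaver | None | Notes on discontinuers (2.15); clinician ratings if the participant comes to the visits |
| Home practice, including after the missed-session email | None | Volunteered reports only; clinician ratings for psychiatric change |

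The clinician ratings (PANSS, CGI, CDSS) measure psychiatric state. None asks about injury, falls or other physical harm.

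**The case against.** The strongest case against is that silence in a condensed article is being read as a rule. Section 5 does not say that the instructors' question is the only one. Sections 4 and 5 allow any event related to participation to be recorded, and neither excludes home practice, session 24 or discontinuers. The wording of missed-session contacts and the content of discontinuation notes are details that a full protocol could hold. Clinicians rate symptoms at week 5–7 and week 12 at visits separate from the sessions. Section 2.15 promises to assess treatment changes, including in patients who become ill. Interviewees are chosen partly for variation in participation rate. Table 2 has no harm endpoint, so there is no planned comparison to bias. The Discussion reports high attendance and no dropouts in the pilot.

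Much of this stands, and it rules out several stronger readings that a reader might infer:
- **That harms causing absence go unrecorded.** Unasked is not unrecorded. Passive reporting exists, and psychiatric worsening may show in the ratings.
- **That every missed session loses harm information.** Someone who misses one session and returns can be asked then. Any figure for missed sessions would also rest on an attendance rate that the article does not give.
- **That leavers are never asked.** They could be asked at each attended session after their first. Only the last one is out of reach.
- **That all 30 go unasked after session 24 in addition to the leavers.** Those who left earlier did not attend session 24.

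What does not stand is the appeal to condensation. The article has its own safety section and fixes a method of enquiry there; section 2.13 fixes a response to absence. The two do not meet. The pilot had two participants and says little about attendance in 30. A count will exist even without a harm endpoint, because section 5 undertakes to record events and grade their severity.

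**Conclusion.** The point holds as a limited gap in how harms are ascertained. The only active enquiry stated misses session 24, the last attended session of anyone who stops coming, and all home practice. What is left uncovered is chiefly injury and other physical harm. The intervention-arm count depends on attendance, and it is likely to be too low if events that nobody asks about are reported less often than those asked about.

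The bound of 23 of 24 sessions needs only the wording of section 5 and the fact that instructors meet participants at sessions. The figure of 7 or 8 of 30 needs the two dropout assumptions given in the check. The number of missed or home sessions affected is unknown. The change is worth making because it is nearly free and improves on a method that the article itself fixes.

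**What to change.** - Put the same brief harm question to both arms at the existing week 5–7 and week 12 visits, including participants who have stopped attending. Word it for the intervention arm so that it covers sessions and home practice. Ask both arms because section 5 directs its question to intervention participants only, and adding visits for that arm alone would widen the imbalance. Section 2.11 places the final tests within 1–2 weeks after the intervention ends, so a question there also reaches session 24.
- Ask the reason for absence in the missed-session contact that section 2.13 already makes.
- Record the reason for each discontinuation in the notes that section 2.15 already promises.
- Reconcile sections 2.13, 2.15 and 5 on how absence and home practice are handled. This review proposes no rule on when exercise may be encouraged; that is for the investigators.

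The cost is a few minutes per patient and a somewhat higher reported event count, which should be expected when more people are asked.

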### 2.14. Tailoring and modification

After the pilot study, which was conducted in spring 2023, the intervention is modified if needed, to suit the needs of the participants based on the remarks made during the pilot study. To address individual differences and to give easy-access modifications when needed, the components will be introduced in steps with sensitivity to the group needs with a central aim to make the participants feel included regardless of previous experience. For those who need extra instruction and support, one of the instructors will be able to assist.

### 2.15. Adherence

Intervention adherence will be noted by the instructors during both pilot study and main study. To stimulate high adherence to the intervention throughout all the intervention time period, we will work in close collaboration with the clinic, both for reminding about the importance of intervention participation during the 12 weeks and in practical issues regarding getting to the studio in time. To keep the creative physical exercise sessions motivating and interesting, the focus will be on enjoyment, social inclusion and increasing body movement in harmony with music. In addition, the fact that the intervention consists of three different parts with separate themes will hopefully stimulate adherence motivation. To retain as many participants as possible, reminder text-messages and emails will be sent to participants. Notes about participants who discontinue or deviate from the study will be made.

Randomization will minimize bias, but we will assess any change in the treatment plan of the participants including medication, if they stop taking their medication and become ill, or if they change to a better medication and improve because of the intervention.

## 3. Outcomes

This study includes neuroscientific and physiological measures, questionnaires (for the patients in the study and their family member or other next of kin), and qualitative interviews (with both the patients in the study and their family member or other next of kin; Table 2). The questionnaire sessions are performed at the Örebro University Hospital, and the project team provides assistance. The measures include PANSS, CGI-s, CGI-I and EQ-5D-L, PSP, and CDSS are needed to measure change in symptom presentation (PANSS), disease severity (CGI-S) and changes in that improvement (CGI-I; Busner and Targum, 2007), improvement in social functioning (PSP), quality of life (EQ-5D-L). The explorative results cover the subjective experience of the patients and their related parties regarding the participation in the intervention (qualitative interviews). See Table 2 for the timeline of the data collection of all outcome measures.

**TABLE 2 T2:** Enrollment, interventions, and assessments.

Testing occasion	Baseline, 2–4 weeks before intervention approx. 150 min	Week 2 (session 2) approx. 60 min	Week 6 (session 12) approx. 60 min	Sometime week 5–7 approx. 60 min	Week 12 (session 23) approx. 60 min	Week 12 approx. 150 min	Month 6 and 12 (longtime follow up) approx. 150 min
**Primary outcome measure**							
PANSS negative symptoms subscale	V, O two items			V, O two items		V, O two items	V, O two items
**Secondary outcome measures**							
General PANSS and positive symptoms subscale (45 min)	V, O two items			V, O two items		V, O two items	V, O two items
CGI-S and CGI-I (5 min)	V			V, O for CGI-I		V, O for CGI-I	V, O for CGI-I
CDSS (10 min)	V			V		V	V
PSP (10 min)	V			V		V	V
Burden of care, VAS (5 min)	O			O		O	O
BAQ-sv, 10 min	X			X		X	X
EQ-5D-5L, 5 min	X			X		X	X
Weight, length, BMI, 5 min	X			X		X	X
Waistline, 1 min	X			X		X	X
Blood pressure, 10 min rest, 2 min test	X			X		X	X
Resting pulse, 1 min	X			X		X	X
Breathing frequency, 1 min	X			X		X	X
Postural stability/balance, 10 min	X			X		X	X
Chair stand test, 3 min	X			X		X	X
fNIRS-EEG combined with eye tracking during cognitive paradigms including STROOP, verbal fluency, AX-continuous performance test, Emotion regulation test. 45 min	X					X	X
Everyday activity/accelerometer	X (measured at home, 7 days)					X (measured at home, 7 days)	
Motion Capture 60 min		X	X		X		
**Exploratory outcome measures**							
Interview, 60 min						X, O	

An “X” represents a patient report, an “O” represents a family member or other next of kin report, and “V” represents a clinician report.

